## Abstract

**Introduction:**

Preventive counseling improves long-term health, but primary care clinicians face time constraints limiting patient education. In a prior emergency department pilot study, a brief *passive* video trended towards increased patients’ willingness to change health behaviors. The current trial, conducted at the primary care clinic, evaluates the feasibility and impact of a short, *interactive* prevention video delivered during a primary care office visit.

**Methods and analysis:**

We will conduct a prospective, randomized, non-blinded clinical trial among adult patients presenting to a primary care clinic. Immediately after their appointment, participants will be randomized to receive either the interactive prevention video or usual care. The video maintains engagement through simple in-video questions and adapts content based on patient responses (e.g., skipping smoking cessation for non-smokers). After the encounter, all participants will complete surveys assessing readiness and confidence to initiate lifestyle change including a transtheoretical “readiness ruler.” Survey items will be drawn from validated instruments, including the Gillespie & Lenz Readiness and Confidence to Participate in Lifestyle Activities Surveys, the Pittsburgh Sleep Quality Index (PSQI), and select questions from the U.S. Hospital Consumer Assessment of Healthcare Providers and Systems (HCAHPS) Survey. Patients will be asked for medical record access and permission for follow-up contact.

**Outcomes:**

The primary outcome is index-visit Lifestyle Readiness and Confidence to Change scores. Secondary outcomes include satisfaction with the clinic visit, intention to change specific lifestyle behaviors, and healthcare use outside the clinic at 30 days and 6 months, as assessed via record review. A 3–12-month follow-up survey will assess self-reported lifestyle changes and new diagnoses.

**Statistical plan and sample size:**

Analyses will follow intention-to-treat. Ordinal logistic regression will compare primary outcomes between arms, adjusting for Charlson Comorbidity Index, age, sex, gender, and prespecified predictors. Logistic regression will evaluate binary follow-up outcomes. Complete-case analyses will be used, and differential attrition will be reported. We plan to enroll approximately 350 patients.

**Trial registration:**

ClinicalTrials.gov NCT06730737.

## Introduction

Preventive measures are critical in avoiding and limiting the severity of diseases. It is intuitive and widely accepted that preventing disease is much more potent than treating morbidities once they have developed. It has been estimated that health behaviors contribute as much as four-fifths of health outcomes, which can be attributed to behavioral and social factors, with clinical care only contributing a small proportion of influence [1,2]. This implies that the clinical encounter should always promote behavior changes, emphasizing prevention. However, contemporary healthcare is characterized by scheduling efficiencies emphasizing shorter times spent in direct contact between the provider and the patient. Direct observations of primary care practices have noted that prevention is under-emphasized [3]. Various reasons have been given for the lack of time for lifestyle change counseling. It is thus implicit that new methods are needed to educate patients about self-care and prevention that require less of a clinician’s time.

This project will evaluate the impact of a video-based educational intervention administered in the primary care clinic following the practitioner’s first encounter with the patient. It will also endeavor to examine the feasibility and efficiency of introducing patients and their accompanying family members to the importance of adopting changes in lifestyle behaviors.

Receptivity to health behavior changes has been extensively investigated. The transtheoretical model is a highly used measurement of receptivity to change and may be used to optimize intervention [4]. This model relates that there are six stages people fall into when adopting a more healthful lifestyle. The first stage is *pre-contemplation,* in which people have no plans to take action to change their behavior in the near future. This may be due to a need for more information or previous unsuccessful attempts to change. *Contemplation* occurs when people want to change their behavior within the next six months. They may be more aware of the benefits and costs, but this awareness can create trepidation and cause people to remain in this stage for extended periods. The third stage is *preparation*, defined as an individual’s readiness to change their behavior within the next month. They have a plan and are ready for an action-oriented program. The following stages include *action,* where changes are initiated within the last six months; *maintenance,* where people continue positive behaviors and work to prevent relapse; and *termination,* where people have no temptation to return to their old behavior. The transtheoretical model is often applied to preventive behavioral change. For example, it was reported that current smokers typically fall into a spread of 40% pre-contemplation, 40% contemplation, and 20% preparation [4]. This research suggests that when faced with the potential for serious adverse health outcomes, patients may be able to accelerate through some early stages, such as moving from pre-contemplation to contemplation or onto the preparation stage.

There have been previous attempts to implement prevention and education in the primary care clinic. These attempts include written after-visit summaries (AVS) shared with the patient. However, it has been reported that the AVS is not the most effective tool, considering that only 82.8% of patients recalled receiving an AVS, and 67.4% of patients consulted their AVS [5]. The information provided in the AVS is typically specific to the reason for that visit and includes contact information for a follow-up appointment. Another study measured whether patients given the AVS have better or worse glaucoma medication recall and revealed that 51.2% did not recall receiving any AVS. Those who recalled receiving one paradoxically had *lower* medication recall scores (remembering the name or color of the bottle or cap, treatment eye(s), and dosing regimen) than those who did not [6]. These results show that the intended goal of printed AVS, which is to enhance patient care, fails to be consistently achieved.

Moreover, there have been previous attempts at smoking cessation education in the primary care clinic. One example of these studies consisted of a training program focused on motivational interviewing to reduce smoking among adolescent patients. Follow-up assessments were conducted at 1, 3, and 6 months post-interview [7]. It was reported that abstinence rates at the 6-month follow-up were significantly higher in the motivational interview group compared to the standard advice control group [7].

Innovative approaches are needed to help patients absorb and retain the information required to properly ensure a healthy future. Showing a video on ways to enhance health while the patient is in the primary care provider (PCP) office could be an effective medium. In one study, patients who watched videos while they were waiting to be seen resulted in a higher proportion of patients rated their stay as “excellent” or “very good” (65%) in comparison to those who were not shown a video (58.1%) [8]. Those who received the video discharge instructions tested better on a post-test survey than the standard instructions group [9]. Another smaller study showed that after viewing an educational video on myocardial infarction, participants in the group shown the video had statistically significant improvement in the results of their knowledge assessment compared to the group not shown the video. The intervention group had a mean number of correct responses of 27 out of 37 questions as opposed to 20 in the control [10]. This supports the use of video as a practical approach to preventive education.

### Objectives

Primary objective: This study will evaluate the utility of presenting patients attending a primary care clinic with a focused video that will expose them to evidence-based education based on four of the core “pillars of preventive lifestyle health” promulgated by the American College of Lifestyle Medicine [11], including successful strategies for diet, exercise, sleep hygiene, and smoking cessation (S4 Appendix D).

### Study hypotheses

We hypothesize that patients receiving the interactive video intervention will exhibit greater readiness and confidence to change lifestyle behaviors compared to patients in the control group, as measured immediately post-intervention.

Null hypothesis (H₀): There is no difference in readiness and confidence to change lifestyle behaviors between the intervention group and the control group.

Alternative hypothesis (H₁): The intervention group will demonstrate significantly greater readiness and confidence to change lifestyle behaviors than the control group.

## Materials and methods

This will be a randomized, controlled, unblinded, two-armed superiority clinical trial. The study will be conducted according to the Standard Protocol Items: Recommendations for Interventional Trials (SPIRIT) Checklist (see S5 Checklist SPIRIT Checklist). The study was approved by Trinity Health at Ann Arbor Institutional Review Board (IRB number: E-24–1117). The trial was prospectively registered in the Clinicaltrials.gov database (registration number: NCT06730737).

The study’s primary outcome will be the results from the Lifestyle Readiness to Change and Confidence to Change questionnaires, both of which use a *readiness ruler* (see S2 Appendix B) [12]. The intervention will include four primary prevention domains promulgated by the American College of Lifestyle Medicine: diet, exercise, sleep hygiene, and smoking cessation.

Secondary aims include:

1)To evaluate the ability to implement a preventive education strategy in the primary care clinic setting2)To assess the impact of age on willingness to change lifestyle behaviors3)To determine characteristics of those receiving the video concerning patient satisfaction, utilizing select Hospital Consumer Assessment of Healthcare Providers and Systems (HCAHPS) Survey questions, compared to the control group

### Eligibility

Inclusion criteria:

All adults, including all ethnicities and genders, between the ages of 18 and 80 who come into the primary care clinic will be recruited to participate in the study.

Exclusion criteria:

Non-English-speaking patientUnable or unwilling to consent to the studyUnable or unwilling to hear a video on a smartphone or computer tabletThe patient is in hospice carePatients with advanced dementia, incapable of answering the survey questions in the opinion of the person administering the surveyNote: Research associates will consult the patient’s primary practitioner or the physician members of the research team for any questions regarding dementia.

Note:

There are no relevant concomitant care activities or interventions that are permitted or prohibited during the trial.

### Participant enrollment and screening

Adult patients aged 18–80 will be recruited by a study team member or a research associate before their appointment or upon arrival at an Academic Internal Medicine ambulatory clinic. Please see the flow diagram for the randomization process and the table for the study process (Fig 1 and Table 1).

**Table 1 pone.0322244.t001:** Schedule of enrollment, interventions, and assessments.

	STUDY PERIOD				
	Enrollment	Allocation	Post-allocation		Close-out
TIMEPOINT	-t_1_	0	t_1_ (time 0)	t_2_ (3–12 months)	t_x_
ENROLLMENT:					
Eligibility Screen	X				
Informed Consent	X				
HIPAA Waiver	X				
Randomization/Allocation		X			
INTERVENTIONS:					
Watch Video			X		
Standard-of-care			X		
ASSESSMENTS:					
Baseline Assessment*	X				
Primary Outcomes**			X		X
Secondary Outcomes***			X		X
Follow-up Survey				X	X

*Sociodemographic, clinical, and lifestyle characteristics.

**Readiness/Confidence to Change questionnaires.

***Satisfaction with the primary care clinic visit and others.

**Fig 1 pone.0322244.g001:**
[figure not shown]
Flowchart for the study process. Note that all videos will use the interactive format. Patients will not be video recorded.

The randomization module within Research Electronic Data Capture (REDCap) will be used to allocate the video intervention. Those randomized for the intervention will be asked if they are interested and willing to watch a video about the clinic visit and their health. Those who agree to watch will then interact with a video featuring lifestyle changes relating to diet, exercise, sleeping, and smoking and why they are important for one’s overall health. The media is interactive because it contains questions for the user to answer at different points within the video sequence. The control group will not watch the video.

The study includes two surveys: the first will be administered in the clinic, and the second will be a follow-up survey administered upon phone contact with consenting patients. Target follow-up is planned for 3–12 months following the initial visit.

Whether receiving the video intervention or not, all participants will have provided verbal consent to answer the questionnaires (see the included script at the heading of the initial survey instrument within S2 Appendix B). They will then fill out the questionnaire at the end of the video either alone, with the assistance of an accompanying relative, or with the assistance of a research team member to determine their stage of the transtheoretical model. A study identification number will be placed on the completed survey. The ID number and the patient’s identifying information will be noted in REDCap. Any patient who declines to participate will not have their patient health information (PHI) included in the study. The REDCap file containing the patients’ personally identifiable information will be kept on password-protected servers using the institution’s REDCap.

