### Study procedures

Research associates and/or research team members will screen for eligible patients using a screening form based on the inclusion/exclusion criteria mentioned above. Results will be analyzed at two stages: first, with the results of the questionnaires administered as part of the initial visit, and second, after concluding the 3–12 month follow-up survey. The consent, educational video, and questionnaire will all be conducted while the patient is in the waiting room, after the clinician (physician or advanced practice provider) has completed the initial patient encounter, or after the provider contact has been completed.

The patients will fill out the composite questionnaire. This questionnaire is designed with the following criteria: prioritize using validated tools capable of self-administration. The Readiness-to-Change questionnaire evaluates patient readiness to implement ten lifestyle behaviors based on a 5-point rating scale. A rating of 5 represents having no interest in the suggested lifestyle change, which is consistent with the precontemplation stage of the transtheoretical model (TTM). A rating of 4 means an interest in implementing the lifestyle change in the next few months (contemplation stage of the TTM). A rating of 3 represents having the plan to implement the lifestyle change within the next month (preparation stage of the TTM). A rating of 2 represents having already started the lifestyle change within the past few months (action stage of TTM). A rating of 1 means having maintained lifestyle behavior changes for over 6 months (maintenance stage of TTM). The Confidence-to-Change questionnaire evaluates patient confidence in implementing the same lifestyle behaviors as the Readiness-to-Change questionnaire. However, the Confidence-to-Change questionnaire is based on a 3-point rating scale. Ratings are as follows: 3-very confident, 2-somewhat confident, and 1-not very confident [12]. The Confidence-to-Change questionnaire addresses any barriers or hesitancy that may impact patient confidence in implementing better lifestyle behaviors. Additional questions will include measures of satisfaction taken from the HCAHPS, specifically addressing their practitioner and visit (S2 Appendix B).

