Sometime after the visit (target: 3–12 months later), they will receive a phone follow-up call, asking them if they have adopted any lifestyle changes since watching the video, among other inquiries (S3 Appendix C). We will use patients’ responses at this later stage (follow-up phase) to help determine how sustainable the preventive education intervention has been.

Randomized patients who participate in the study will receive the video intervention. In a previous pilot study, we investigated the impact of a simple instructional video on patients’ willingness to change in the emergency department setting [13]. The initial intervention was passive, requiring subjects to watch a video without interaction. The current study evaluates the practicality and impact of bringing a brief *interactive* educational video intervention to patients attending the primary care clinic visit.

All patients, including those randomized to “no video learning,” will be asked to complete a questionnaire. The questions will be administered orally or self-administered for those willing to participate using the tablet interface. Responses will be recorded using REDCap electronic data capture software and the related platform.

A sample size of approximately 350 was chosen based on feasibility and the expectation of sufficient power to detect moderate differences in readiness and confidence scores, guided by prior pilot study results. Due to the minimal risks in this study, a data monitoring committee is not considered necessary. An interim analysis will be conducted after 200 patients have been enrolled. It is anticipated that the total data collection will take six months. For those patients who agree to receive a call-back, contact will be attempted during the 3–12-month follow-up period. A research associate, a resident, or an attending physician will complete the follow-up by telephone or email correspondence with the subject. Up to 3 follow-up attempts will be made. Available follow-up data from the interactive electronic health record (EHR) will be obtained on all patients. The estimated time to view and interact with the video is approximately 10–15 minutes. The time required for responses to the survey component is estimated at 10–12 minutes.

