### Statistical methods

The study team members will collect demographic data upon registration to the patient’s clinic. Patients from ages 18–80 will be included in the study. After informed consent, patients will be randomized to either the intervention or the control arm of the study. Only the interventional arm will interact with the video using a provided computer tablet which focuses on lifestyle preventive education. Control patients will not receive a video and will go directly to the follow-up questionnaire. Hence, both groups will receive the follow-up survey from research team members.

The Demographic data includes age, sex, gender, race, and insurance status. The patient’s BMI, Charlson Comorbidity Index, smoking status, responses to the social influences of health questionnaires, phone number, and frequency of ED visits will be documented from the patient’s EHR. Their zip code will also be collected for geographic and socioeconomic status analysis (S1 Appendix A).

The study’s primary outcome is the readiness and confidence to change scores as a function of video exposure, measured on a continuous “readiness ruler.” [14].

Secondary outcomes will include readiness to change in specific domains, including exercise, smoking, diet, sleep hygiene, living an overall healthy lifestyle, satisfaction with the hospital, and satisfaction with the practitioner, dichotomized between those who watched the video and those who did not. Part of this data will be obtained directly from the patient’s medical record (S1 Appendix A).

We will collaborate with Michigan Data Analytics, which will provide large-scale data abstraction to assist with obtaining the Charlson Comorbidity Index (CCI) for participating subjects. The remaining data will be collected using the Readiness-to-Change and Confidence-to-Change Lifestyle Questionnaires, the Pittsburgh Sleep Quality Index (PSQI), and U.S. Governmental HCAHPS Patient Satisfaction Survey.

Descriptive statistics will be used to summarize baseline characteristics by study arm, including means and standard deviations for continuous variables and proportions for categorical variables. All analyses will follow the intention-to-treat principle.

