## Regulatory requirements

### Informed consent

All patients will be consented. Informed consent will be obtained before the randomization of subjects. If they approve, the research team member will administer the informed consent form within the supplementary information of this protocol.

Those who approve to watch the interactive video will be given a QR code to watch on their smartphone or a tablet with a link to the video, which the patient or the research team member may start.

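### A second willingness question, put to the video arm alone after allocation, overlaps an exclusion criterion, and the protocol does not fix how patients who then refuse are analysed

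*Protocol article*

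**What the plan says.** All locations are in the protocol article.

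- **Eligibility** excludes patients who are unable or unwilling to hear a video on a phone or tablet. This applies to every patient, whatever the arm.
- **Study procedures** says that staff "will screen for eligible patients using a screening form based on the inclusion/exclusion criteria mentioned above". Table 1 puts the eligibility screen and consent under enrollment, ahead of allocation, and Informed consent confirms that "Informed consent will be obtained before the randomization of subjects".
- **Participant enrollment and screening** (text below Fig 1) describes REDCap allocation and then says: "Those randomized for the intervention will be asked if they are interested and willing to watch a video". It continues: "Those who agree to watch will then interact with a video". No matching question is described for controls. Informed consent likewise gives the video link to those who approve watching.
- **Study procedures** reads differently: "Randomized patients who participate in the study will receive the video intervention".
- On data collection, Study procedures says that all patients, including controls, "will be asked to complete a questionnaire". The text below Fig 1 adds: "Any patient who declines to participate will not have their patient health information (PHI) included in the study".
- **Statistical methods** states: "All analyses will follow the intention-to-treat principle". The same section defines the primary outcome in terms of exposure to the video and splits the secondary outcomes by whether the patient viewed it. It uses complete cases and says that no pre-intervention measure will exist.

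**The concern.** A video-arm patient who says no after allocation now appears to meet an exclusion criterion. An equally unwilling control is not asked again. The protocol does not say whether the first patient is a protocol refuser who stays in the video arm, a late ineligible, or someone who has declined to participate.

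The answer changes the primary comparison. If refusers stay in their arm, the trial estimates the effect of offering the video, and that effect is smaller than the effect of watching it. If they leave the video arm, or are counted with the unexposed, the video group is enriched with patients who were willing to sit through lifestyle advice. The outcome is readiness to change lifestyle, so refusal plausibly tracks low readiness. Without a baseline score, the analysis could not adjust for that selection directly.

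**Working it through.** **1. The passages side by side.** The eligibility list, the screening form and Table 1 imply that willingness is settled for everyone before allocation. The question below Fig 1 is therefore a second ask, in one arm. Its consequence, no video for those who refuse, cannot be squared with the sentence in Study procedures that participating randomized patients receive the video.

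**2. The plan's own figure.** The total of about 350 is justified by feasibility and by power for moderate differences. No effect size, SD, alpha, power or allocation ratio is given, so it cannot be reproduced. For orientation, assume 1:1 allocation (175 per arm), two-sided 0.05, SD = 1 and a normal approximation in place of the planned ordinal model. A difference of 0.30 SD at 80% power then needs 350 in total; 0.50 SD needs 126.

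**3. Refusers kept in the video arm (the stated intention-to-treat plan).** Let r be the share of the video arm that refuses (assumed) and d the effect of watching.

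- Effect by arm = d(1 − r)
- SE = √(2/175) = 0.1069
- Power ≈ Φ(d(1 − r)/SE − 1.96)

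| r | d = 0.30: effect, power | d = 0.50: effect, power |
|---|---|---|
| 0 | 0.300, 80% | 0.500, 99.7% |
| 5% | 0.285, 76% | 0.475, 99% |
| 15% | 0.255, 66% | 0.425, 98% |
| 30% | 0.210, 50% | 0.350, 91% |

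Example: 0.255/0.1069 = 2.385, and Φ(2.385 − 1.96) = 0.66. Type I error is not affected.

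**4. Refusers lost from the video arm only (conditional, not the stated plan).** Take no true effect, and assume that unwilling patients are g = 0.5 SD less ready.

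- False difference = r·g
- SE = √(1/175 + 1/[175(1 − r)])

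At r = 15%: 0.075 SD, SE 0.1115, two-sided rejection rate about 10%. At r = 30%: 0.150 SD, SE 0.1178, about 25% (about 24% if the extra variance from mixing willing and unwilling controls is included).

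**5. Grouping by watched or not watched (conditional).** Refusers join the comparison group, where the unwilling share becomes 2r/(1 + r).

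- False difference = g·2r/(1 + r)
- At r = 15%: 0.5 × 0.30/1.15 = 0.130 SD
- At r = 30%: 0.5 × 0.60/1.30 = 0.231 SD

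On the same assumptions, this is a larger distortion than in step 4.

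**The case against.** The strongest defence is that the protocol already covers both halves of the problem. Willingness is an exclusion criterion on a pre-allocation screen, so the later question goes to patients already screened as willing, and refusals should be fewer than in an unscreened sample. Intention-to-treat is stated for all analyses and every patient is asked for the questionnaire, so refusers remain in the video arm and the result is ordinary non-adherence, which is conservative. Feasibility is an aim of the trial, so uptake after an offer is informative, and a participant may always decline.

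Much of this stands, and it rules out several stronger readings:

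- *Willingness is asked only after allocation and only in the video arm.* Not supported: the screening form and Table 1 place the criterion earlier, for everyone.
- *The plan drops refusers, so its type I error is inflated.* Not supported: no passage says so. The sentence "Any patient who declines to participate will not have their patient health information (PHI) included in the study" follows the text on consent to the questionnaires and most naturally concerns people who decline the study, although it does not separate that from declining the video.
- *The dementia exclusion has the same flaw because the person giving the survey judges it.* Not supported: that wording says who judges, not when, and the criterion falls under the same pre-allocation screen.

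The defence does not answer the conflict over who receives the video. Nor does it answer the exposure-based outcome wording, which sits in the same section as the intention-to-treat statement and contradicts it. A refuser who skips the questionnaire would still be lost as an incomplete case. The feasibility aim does not need the gate: refusals after allocation can be recorded and reported as non-adherence.

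**Conclusion.** The point holds as an inconsistency that should be fixed. The document places a willingness question in one arm after allocation, contradicts itself on who receives the video, and describes outcomes both by randomized arm and by exposure.

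Under the stated intention-to-treat principle the consequence is dilution. It is material if the true effect is near 0.30 SD and refusal reaches 15% to 30%, and minor if the effect is near 0.50 SD. Selection bias is a conditional risk: it follows only if the exposure wording governs the analysis, if refusers drop out of the complete-case set, or if declining the video is treated as declining the study.

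All sizes rest on assumed refusal rates, effect sizes, allocation ratio and alpha, and the bias figures also on an assumed 0.5 SD gap. The protocol supplies none of these. The contradictions themselves need no assumption.

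**What to change.** Reconcile Eligibility, Participant enrollment and screening, Study procedures, Statistical methods and Informed consent as follows.

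1. On the pre-randomization screening form, ask every patient explicitly whether they would watch a 10–15 minute video if allocated to it, and apply the exclusion then.
2. Remove the post-allocation willingness question as an eligibility gate. Patients remain free to decline; record this as non-adherence and report it.
3. State that video-arm patients who later decline the video are still asked to complete the questionnaire and are analysed in the assigned arm. Make clear that the sentence on people who decline to participate does not refer to declining the video.
4. In Statistical methods, define the primary outcome comparison by randomized arm, and replace the watched/not-watched grouping of secondary outcomes with the same.

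The cost is one screening question and a few sentences. The small downside is that a few unwilling patients are screened out, as the exclusion criterion already intends. The change needs to be made before enrollment, because a missing pre-allocation answer cannot be recovered afterwards.

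### The self-rated primary outcome of an unblinded trial has no fixed mode of completion, and nothing keeps the person helping with it unaware of the arm

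*Protocol article*

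**What the plan says.** Materials and methods describes the design: "This will be a randomized, controlled, unblinded, two-armed superiority clinical trial". The same section says that the "primary outcome will be the results from the Lifestyle Readiness to Change and Confidence to Change questionnaires". Statistical methods adds that these scores are taken after randomization and that no baseline values will exist.

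Three places describe how the visit questionnaire is completed:

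- The text after Fig 1, under Participant enrollment and screening, says that participants in both arms fill it out "either alone, with the assistance of an accompanying relative, or with the assistance of a research team member to determine their stage". The stage meant is that of the transtheoretical model.
- Study procedures, speaking of all patients including controls, says: "The questions will be administered orally or self-administered for those willing to participate using the tablet interface".
- Statistical methods says: "Control patients will not receive a video and will go directly to the follow-up questionnaire", and continues: "Hence, both groups will receive the follow-up survey from research team members". In context, this is the questionnaire at the visit, not the later telephone survey.

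Two further statements bear on the point. Study procedures gives the design criterion for the questionnaire as "prioritize using validated tools capable of self-administration". Informed consent says that the video is opened from a QR code or tablet link, "which the patient or the research team member may start".

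The article does not set one mode, say who receives which, separate the helper from knowledge of the arm, or state that the mode is recorded. The covariates named in the Abstract do not include it.

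**The concern.** Readiness and confidence are statements of intention, given minutes after a health message or without one. Such answers can depend on who hears them. Two routes lead from the permitted modes to a difference between arms that is not a video effect.

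1. **Influence by a helper who knows the arm.** A team member or relative who knows whether the patient saw the video may prompt, interpret or simply be present in a way that depends on the arm. This can bias the comparison even when equal shares of both arms are assisted.
2. **A different mix of modes by arm.** Nothing fixes the mode before allocation, and only the video arm has just handled a tablet or phone. If the arms then differ in how often they are assisted, any effect of mode enters the comparison.

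Randomization does not protect against either route, because both operate after it. No baseline score is available as a check. Adjusting later for the mode actually used would condition on something that follows allocation, so it is not a clean repair.

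**Working it through.** **The plan's own figure.** The only relevant figure is the total of about 350. It cannot be reproduced, because the article gives no alpha, power, effect size, SD or allocation ratio. For scale, assuming 1:1 allocation (175 per arm), SD 1 and two-sided alpha 0.05, a total of 350 gives 80.1% power for a difference of 0.30 SD. Small biases should be judged against an effect of about that size.

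**Inputs for the illustration.** From the document: about 350 patients. Assumed: 175 per arm, a binary favourable answer given by 50% of controls, and no true effect of the video. The mode shifts and shares below are also assumed; the document gives none.

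**Standard error of the difference.** SE = sqrt(2 × 0.5 × 0.5 / 175) = 0.0535, or 5.3 points.

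**Bias.** False difference = share × shift.

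- For a different mix, the share is the difference between arms in the proportion assisted, and the shift is the change in favourable answers caused by assistance.
- For arm-dependent influence with an equal mix, the share is the proportion assisted, and the shift is the influence acting in the video arm only.

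**Chance of a significant result.** P = 1 − Φ(1.96 − bias/SE) + Φ(−1.96 − bias/SE).

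| Share | Shift | False difference | bias/SE | Two-sided rejection |
|---|---|---|---|---|
| any | 0 | 0 | 0 | 5.0% |
| 20 points | 10 points | 2 points | 0.37 | 6.6% |
| 20 points (or 40) | 20 points (or 10) | 4 points | 0.75 | 11.6% |
| 40 points | 20 points | 8 points | 1.50 | 32.2% |

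**The same check in SD units.** SE = sqrt(2/175) = 0.107 SD.

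- Shift 0.2 SD × share 0.20 = 0.04 SD, rejection 6.6%.
- Shift 0.3 SD × share 0.30 = 0.09 SD, rejection 13.4%.
- Shift 0.5 SD × share 0.30 = 0.15 SD, rejection 28.9%.

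Both scales run from almost no inflation to serious inflation, depending wholly on the assumed inputs. With the same mode in both arms and no arm-dependent influence, the error returns to 5.0%.

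**The case against.** The strongest reply is that the article offers the same options to both arms, chooses tools suited to self-administration, and says that patients fill out the questionnaire. Assistance is then a reasonable accommodation for adults up to 80. The survey script is in an appendix that is not shown, and staff training includes practice in administering the study. Eligibility also excludes, from both arms, patients unable or unwilling to hear a video on a phone or tablet, which weakens the idea that only the video arm is at ease with a device. All of this stands, and it limits the point. It does not answer it: the article itself states the several permitted modes, and being suited to self-administration is not a requirement to self-complete.

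A reader might infer more than the documents support:

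- **That the arms are assigned different modes, or that the mix will differ.** The options are common to both arms, and nothing shows who will choose which. A different mix is possible, not established, and its direction is unknown.
- **That staff decide the patient's stage.** The closing words of "either alone, with the assistance of an accompanying relative, or with the assistance of a research team member to determine their stage" most naturally give the purpose of filling out the questionnaire. Study procedures ties each stage to the patient's own rating.
- **That the person who started the video then takes the answers.** No section says so. A team member may start the video, and team members give the survey, but they need not be the same person.
- **That all desirability bias comes from the mode.** A shift of 5 or 10 points in the video arm alone would give a two-sided error of 15.5% or 46.5%. Part of such a shift would come from patients knowing their own arm and would persist under private completion, so these figures should not be credited to the mode or to its correction.

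The illustration also simplifies: the planned analysis is ordinal, and the low end (6.6% against 5%) is negligible.

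**Conclusion.** The point holds as a cheap, worthwhile improvement to the design. As written, the plan leaves an avoidable route to interviewer and mode bias in its primary outcome: a self-rated measure without a baseline, in an unblinded trial, may be answered to or through people who know the arm. The route through arm-aware helpers does not depend on any difference in mix; the route through mix is only a possibility.

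The size is unknown. With 175 per arm, 50% favourable control answers, a binary outcome and no true effect, false differences of 2 to 8 points would raise the two-sided 5% error to about 7% to 32%. These figures show sensitivity to assumed inputs; they are not an estimate of what will happen.

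**What to change.** Amend the questionnaire text after Fig 1 and the matching text in Study procedures, as follows:

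- Make private self-completion on the REDCap tablet the default for the readiness and confidence items in both arms. Staff and relatives should neither view nor discuss the answers.
- Allow assistance or reading aloud only for patients who cannot self-complete, with that need recorded before randomization.
- Record the mode actually used and report it by arm.
- Add a sensitivity analysis in patients identified before randomization as able to self-complete. Because this group is defined before allocation, the randomized comparison within it is preserved.

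The cost is a wording change and a small addition to REDCap for the need for help and the mode used; the tablet and suitable instruments are already in the plan. Mode that is not captured at the visit cannot be reliably recovered later.

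The downside is possibly a few more skipped items. That matters somewhat, because the analysis is complete-case without imputation, but tablet prompts for missed items can limit it. The change removes the avoidable part of the bias only: patients will still know which arm they are in.
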